### ***8.3 Criteria of exclusion from data analysis***

Participants who should not be enrolled but have been enrolled, or who have completed the study but have violated some provisions of the study protocol, should be excluded from data analysis according to the investigator, including:

- (1) Those who have not used the prescribed medication.
- (2) Those without any test results after medication.
- (3) Those in whom, due to the use of forbidden drugs, the efficiency and safety cannot be evaluated.

At the blinded review meeting, the principal investigator and statistician will decide whether to eliminate cases and what data set to enter. The reasons for the exclusion should be explained, and their medical notes should be retained for future reference.

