## **XI. Statistics**

### **1. statistical considerations**

The intention to treat (ITT) principle will be applied in analyses as the full analysis set. Full analysis set: according to the basic principle of (ITT) analysis, all randomized subjects with more than one medication record and effectiveness evaluation will be included in the full analysis set. In the analysis of the full analysis set, the carry forward estimation method of the latest observation can be used for the estimation of missing values. The full analysis set is the main effectiveness evaluation population of this study.

In addition, this study will also establish a per-protocol (PP) set: including all subjects who complete the treatment specified in the protocol or do not have major protocol violations. The definition of major protocol violation will be finalized at the time of data review, which may generally include the following cases (but not limited to these

cases): serious violation of the inclusion criteria, treatment that seriously interferes with the efficacy evaluation after enrollment, serious violation of the medication dosing scheme, loss of the primary efficacy evaluation, etc.

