## **4. Primary outcome and sample size estimation**

This study is a 1:1 randomized controlled trial. The study group is the tirofiban combined with thrombectomy group, and the control group is the routine thrombectomy group. The primary outcome of the study is a composite outcome: the probability of first-pass recanalization of targeted vessels without increasing the risk of symptomatic intracranial hemorrhage. The Chi-square test is used to compare the primary endpoint between groups.

According to the retrospective analysis of the International Stroke Perfusion Imaging registry (INSPIRE <https://taste.newcastle.edu.au/key=inspire>) participated in by the research team, the proportion of patients who achieved first-pass recanalization without

symptomatic hemorrhage using intravenous tirofiban before thrombectomy was 71% (94/132), while the rate of patients who achieved first-pass recanalization without symptomatic hemorrhage in direct thrombectomy was 48% (55/115).

The conservative estimate for this project is that the rate of primary outcome will be 70% in the study group and 50% in the control group. With two-sided  $\alpha=0.05$ , power=80%, assuming a 7% dropout rate, the final sample size is 100 subjects in the study group and 100 subjects in the control group, or 200 subjects in total, which was calculated using Stata 13.0 software.

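### The per-protocol set is defined with 'or' where 'and' is needed, so major violators who completed treatment stay in, against section 8.3

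*Protocol*

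**What the plan says.** Protocol, XI. Statistics, 1. statistical considerations, sets up two populations. On the first it says: "The full analysis set is the main effectiveness evaluation population of this study". The second is the PP set, described as "including all subjects who complete the treatment specified in the protocol or do not have major protocol violations".

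On violations the section adds: "The definition of major protocol violation will be finalized at the time of data review". It introduces its examples as open-ended: "may generally include the following cases (but not limited to these". There are four:
- a serious breach of the inclusion criteria;
- treatment after enrolment that seriously disturbs the efficacy assessment;
- a serious departure from the dosing scheme;
- a missing primary efficacy assessment.

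Protocol, VI. Methods, 8.3 (criteria of exclusion from data analysis), covers wrongly enrolled participants and also those who "completed the study but have violated some provisions of the study protocol, should be excluded from data analysis according to the investigator". On who decides, it says: "At the blinded review meeting, the principal investigator and statistician will decide whether to eliminate cases and what data set to enter". Section 6.3 places database lock after the blinded review.

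**The concern.** A PP set is meant to hold the patients who received the assigned treatment and had no serious departure from the protocol, so it needs both conditions. Joining them with 'or' makes either one sufficient. Once a patient has completed treatment, none of the four listed violations can remove that patient, so the list that follows the definition has almost no work to do.

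The PP set is the only alternative analysis population that this protocol names. If it removes very few patients, its result will resemble the full-analysis-set result whatever the adherence. A reader could then take that similarity as evidence that violations did not matter, when most of the violators were never taken out. A programmer who follows the sentence as written would build this set.

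**Working it through.** **Effect on the plan's own figure.** Inputs from XI. Statistics, 4: 70% against 50%, two-sided 5% level, "power=80%, assuming a 7% dropout rate". With a pooled variance and no continuity correction:

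n per arm = [1.960 × √(2 × 0.6 × 0.4) + 0.8416 × √(0.7 × 0.3 + 0.5 × 0.5)]² / 0.20² = (1.358 + 0.571)² / 0.04 ≈ 93; 93 / 0.93 = 100.

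This reproduces 100 per arm and 200 in total. The PP set does not enter the calculation.

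**What each rule does.**

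| Completed treatment | Major violation | 'or' | 'and' |
|---|---|---|---|
| yes | no | in | in |
| yes | yes | in | out |
| no | no | in | out |
| no | yes | out | out |

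The rules differ in the two middle rows. The second row is the clear error: it keeps completers with a major violation.

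**Against section 8.3.** Take a patient who completed both treatment and study but seriously breached the inclusion criteria or had interfering treatment. XI.1 keeps this patient in the PP set. Section 8.3 excludes the patient from data analysis, without naming the set it means. The two rules give opposite answers.

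**Size.** The documents give neither a non-completion rate nor a violation rate. As an assumption, let 10% of 200 (20 patients) not complete treatment, let 10% (20 patients) have a major violation, and let k patients have both, with k from 0 to 20.

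- 'or' keeps 200 − k.
- 'and' keeps 200 − (20 + 20 − k) = 160 + k.
- Gap = (200 − k) − (160 + k) = 40 − 2k.

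| Overlap | k | 'or' | 'and' | Gap |
|---|---|---|---|---|
| none | 0 | 200 | 160 | 40 |
| independent (200 × 0.1 × 0.1) | 2 | 198 | 162 | 36 |
| complete | 20 | 180 | 180 | 0 |

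Under independence the 36 consist of 20 − 2 = 18 completers with a major violation and 20 − 2 = 18 non-completers without one.

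**Other assumed shares, independence kept.** Let c be the share completing treatment and v the share without a major violation. Then 'or' = 200(c + v − cv), 'and' = 200cv, and completers with a violation = 200c(1 − v).

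| c | v | 'or' | 'and' | Completers with a violation |
|---|---|---|---|---|
| 0.85 | 0.85 | 195.5 | 144.5 | 25.5 |
| 0.85 | 0.95 | 198.5 | 161.5 | 8.5 |
| 0.90 | 0.90 | 198 | 162 | 18 |
| 0.95 | 0.85 | 198.5 | 161.5 | 28.5 |
| 0.95 | 0.95 | 199.5 | 180.5 | 9.5 |

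Across this range the literal rule removes fewer than 5 of 200 patients.

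**The case against.** The strongest reply is that 'or' is a drafting slip. A section that lists violations cannot mean to keep the violators, and section 8.3 shows the intent. That is probably right about the intent, but it does not repair the rule. The definition is the text that would be programmed, and nothing in the protocol says that section 8.3 overrides it.

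A second reply concerns the size. A serious dosing violation is one of the listed examples and overlaps with non-completion almost by definition, so independence is only a convenience and the gap shrinks as overlap grows. This stands, and it is why a range is given. Complete overlap is also unlikely, because the other three examples do not depend on whether treatment was completed. Nor can all 36 be called wrongly retained. Eighteen are non-completers without a major violation, and section 7.2 allows the investigator to consider stopping the medication in some situations. Whether such patients belong in a PP set is a matter of definition.

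A reader might also infer that settling the violation list at data review lets cases be selected on outcome in an open-label trial. The documents do not support this. Section 8.3 puts the choice of data set at a blinded review meeting, section 6.3 puts lock after that review, and section 6.2 has recanalization and bleeding read by analysts blinded to group. XIII. Organization promises a detailed statistical analysis plan, where the full list may properly sit.

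**Conclusion.** The definition is wrong as written. It forms a union where a PP set needs both conditions, it empties the violation list beside it, and it conflicts with section 8.3. On the assumed 10% and 10%, the two rules differ by 0 to 40 of 200 patients. Under independence the difference is 36, of whom 18 are completers with a major violation. These figures illustrate the mechanism and do not forecast the trial; both rates and the overlap are assumptions.

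The consequence is limited. A reader might infer that the trial's main conclusion is at risk, but the full analysis set is named as the main efficacy population, and neither the sample size nor the primary test uses the PP set. What is lost is the PP analysis as a view of the effect in adherent patients. This is a minor point, worth correcting because the correction is nearly free.

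**What to change.** In XI. Statistics, 1, replace 'or' with 'and' in the PP definition, so that membership requires both completing the specified treatment and having no major violation. Reconcile this sentence with section 8.3 by stating which analysis set the section 8.3 exclusions apply to, so that a completer with a violation is handled the same way in both places.

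The cost is one word and a cross-reference. The PP set becomes smaller and its confidence interval wider. The sample size of 200 and the primary analysis on the full analysis set stay as they are.

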## **2. General principles**

A superiority test will be conducted in this study. Two-sided  $\alpha=0.05$ , and  $p<0.05$  is considered as a statistical significance threshold. All statistical analyses will be processed with Stata 13.0 or higher statistical software.

## **3. Analysis**

The statistical analysis includes (1) the number of cases completed at each site and the withdrawal of cases; (2) analysis of demographics and baseline characteristics of patients in each group at the time of enrollment, and the comparability between the study group and the control group; (3) efficacy evaluation including the determination of efficacy endpoints and the efficacy comparison of each group; (4) safety evaluation including the comparison of laboratory results and clinical adverse reactions in each group.

## **4. Primary outcome and sample size estimation**

This study is a 1:1 randomized controlled trial. The study group is the tirofiban combined with thrombectomy group, and the control group is the routine thrombectomy group. The primary outcome of the study is a composite outcome: the probability of first-pass recanalization of targeted vessels without increasing the risk of symptomatic intracranial hemorrhage. The Chi-square test is used to compare the primary endpoint between groups.

According to the retrospective analysis of the International Stroke Perfusion Imaging registry (INSPIRE <https://taste.newcastle.edu.au/key=inspire>) participated in by the research team, the proportion of patients who achieved first-pass recanalization without

symptomatic hemorrhage using intravenous tirofiban before thrombectomy was 71% (94/132), while the rate of patients who achieved first-pass recanalization without symptomatic hemorrhage in direct thrombectomy was 48% (55/115).

The conservative estimate for this project is that the rate of primary outcome will be 70% in the study group and 50% in the control group. With two-sided  $\alpha=0.05$ , power=80%, assuming a 7% dropout rate, the final sample size is 100 subjects in the study group and 100 subjects in the control group, or 200 subjects in total, which was calculated using Stata 13.0 software.

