## **VI. Methods**

### **1. Overall design**

This study is a multicenter, prospective, randomized, controlled, open-label, blinded-endpoint study. A total of 200 patients with acute ischemic stroke who are scheduled to undergo thrombectomy will be recruited from 10-15 hospitals in China. They will be randomly assigned 1:1 to the study group or control group. The study design is shown by the following study schema (study design flow chart).

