### **6 Randomization**

#### ***6.1 Randomization procedure***

Patients who meet the inclusion criteria are assigned 1:1 to the study group and control group according to the permuted-block randomization method to ensure the balance between and within the groups. Randomization is stratified by participating sites.

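### Randomization is stratified by site but the named primary test ignores site; a site-stratified test would be a near-free gain if success rates differ between sites (minor)

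*Protocol*

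**What the plan says.** The synopsis and section VI.6.1 of the protocol set 1:1 allocation by permuted blocks, and "Randomization is stratified by participating sites". Site number is the only stratification item in the randomization log (VI.10.2). Section VI.1 plans 200 patients "recruited from 10-15 hospitals in China", which is about 13 to 20 per hospital (200/15 to 200/10).

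Section XI.4 names one primary test: "The Chi-square test is used to compare the primary endpoint between groups". Nothing in the protocol adjusts the primary comparison for site. Section XI.3 mentions sites only for counts of completed and withdrawn cases.

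For the sample size, XI.4 assumes that "the rate of primary outcome will be 70% in the study group and 50% in the control group" and concludes, for a two-sided 5% level: "power=80%, assuming a 7% dropout rate, the final sample size is 100 subjects in the study group and 100 subjects in the control group". Section XI.2 adds that "A superiority test will be conducted in this study".

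**The concern.** Blocking within site makes the two arms nearly equal in size at each hospital, so differences between hospitals largely cancel from the treatment comparison. An unstratified chi-square does not use this. Its variance is that of two simple random samples, so it still counts between-site variation as noise. If sites differ in success rate, the standard error is too large, the test rejects too rarely under the null, and it misses some true effects that a stratified test would detect.

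The protocol gives reasons to think that sites may differ. The endpoint depends on the result of a single device pass (VI.9), the device class is recorded but not mandated (VI.10.4), and apart from the limits the protocol sets, control-arm procedures follow local guidelines (VI.7.2). The sponsor also chose site as its only stratifier. At stake is some statistical efficiency in a trial of 200 patients.

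**Working it through.** **1. Reproduce the plan's figure.** Inputs from XI.4: 50% against 70%, two-sided 5%, 80% power, 7% dropout. The usual two-proportion formula with pooled variance and no continuity correction has mean rate 0.60:

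n = [1.960 × √(2 × 0.6 × 0.4) + 0.8416 × √(0.5 × 0.5 + 0.7 × 0.3)]² / 0.20²
= (1.3579 + 0.5708)² / 0.04 = 93.0, so 93 per group.

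93 / 0.93 = 100 per group. The plan's figure is reproduced exactly, and it belongs to the unstratified test. That test has 80.0% power at 93 per group, and 82.8% if all 100 are evaluable.

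**2. Approximate check of the mechanism.** Under the null at 50%, let V be the variance of the site success rates. The chi-square uses a per-patient variance of 0.25. With balance within sites, the variance that matters is 0.25 − V. The true two-sided error is then the normal tail area beyond 1.96 / √(1 − V/0.25).

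- Logit SD 0.5: site rates have SD about 11.8 points, V = 0.0140, ratio 0.944, cut-off 1.96/0.972 = 2.017, error 4.4%.
- Logit SD 0.75: SD about 16.7 points, V = 0.0279, ratio 0.888, cut-off 1.96/0.942 = 2.080, error 3.8%.
- Logit SD 1.0: SD about 20.8 points, V = 0.0434, ratio 0.826, cut-off 1.96/0.909 = 2.156, error 3.1%.

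**3. Simulation.** Inputs from the protocol: overall rates of 50% and 70%, 10 or 15 sites, site-stratified permuted blocks, and 186 evaluable patients (2 × 93). Assumptions: blocks of 4 (the size is not stated), sites of equal or unequal size, and normal site effects on the logit scale. There were 20,000 trials per cell, so the Monte Carlo standard error is about 0.15 point for type I error and 0.3 point for power. The ranges cover 10 and 15 sites and both size patterns. CMH is the Cochran-Mantel-Haenszel test by site, without continuity correction.

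| Site SD (logit) | Type I, chi-square | Type I, CMH | Power, chi-square | Power, CMH | Change in power (points) |
|---|---|---|---|---|---|
| 0 | 4.6–4.9% | 4.7–5.1% | 79.5–79.9% | 79.0–79.8% | −0.5 to −0.1 |
| 0.3 | 4.5–4.9% | 4.8–5.2% | 80.3–80.6% | 80.2–81.1% | 0 to +0.5 |
| 0.5 | 4.2–4.5% | 4.9–5.0% | 80.7–80.8% | 81.6–82.1% | +0.8 to +1.3 |
| 0.75 | 3.8–4.1% | 4.9–5.3% | 81.1–81.5% | 83.6–84.2% | +2.3 to +2.9 |
| 1.0 | 3.3–3.5% | 5.0–5.2% | 81.4–82.2% | 86.0–86.5% | +4.1 to +4.6 |

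A separate run with unequal sites and 8,000 trials per cell gave chi-square type I errors of about 4.3%, 3.8% and 3.1–3.4% at SD 0.5, 0.75 and 1.0, with the same power gains. The approximation in step 2 agrees.

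**4. What the assumed spreads mean.** Around a 50% rate, the central 95% of site rates runs from 1/(1 + exp(1.96 × SD)) to its complement: about 27–73% at SD 0.5, 19–81% at 0.75 and 12–88% at 1.0.

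**The case against.** The strongest reply is that nothing in XI.4 is computed wrongly. The 100 per group was sized for the unstratified test, and that test stays at about 80% or above in every scenario examined. A reader might infer that the trial is underpowered or has lost power that its sample size was meant to secure. The documents do not support that, because the planned power is delivered.

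The loss is also conditional. No section gives the variation in first-pass success between hospitals. Sites must have acute stroke units and thrombectomy experience (IX), and investigators are trained and assessed before starting (IX.3), so the widest spreads may be unrealistic. If sites do not differ, stratifying over 10 to 15 small groups costs up to half a point. All of this stands, and it keeps the point minor.

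It might also be said that a separate analysis plan, promised in the section on the data safety monitoring board (XIII), can deal with site. That holds for supportive covariate models, and their absence here is no defect. It does not hold for the primary test: the protocol names one, and a plan that made a stratified test primary would then conflict with XI.4.

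**Conclusion.** This is a free improvement of minor severity. The randomization uses site and the named primary test does not. If site success rates differ, the chi-square is conservative. The power forgone is about 1 point at a logit SD of 0.5, 2.5 at 0.75 and 4 to 5 at 1.0, and nothing when sites are alike. These figures rest on an assumed between-site spread, an assumed block size of 4 and 186 evaluable patients.

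A reader might infer that the mismatch makes the primary result unreliable. It does not: the error is in the safe direction, and type I error stays below 5%. The case for changing is that the possible gain is several times the possible loss, and that site is already recorded for every patient.

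**What to change.** In section XI.4, replace the chi-square as the primary analysis with a Cochran-Mantel-Haenszel test stratified by randomization site. Report the Mantel-Haenszel risk difference with its 95% confidence interval. Pool very small sites by a rule fixed before unblinding. Keep the unstratified chi-square as a sensitivity analysis. If the sponsor prefers to keep it as primary, XI.4 should say why site is ignored.

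The cost is a sentence or two in the protocol, matching text in the statistical analysis plan and negligible programming. The sample size need not change. The statistical downside is up to about half a point of power if sites do not differ.

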### ***10.2 Randomization assessment***

All patients with acute ischemic stroke due to large artery occlusion will be assessed for eligibility for the study using a checklist of the criteria described previously. The enrollment and randomization log should be kept in a locked filing cabinet within each participating center.

The log should include:

- Patient demographic information: sex, date of birth, time of onset (or last seen without symptoms), time of admission, NIHSS before randomization, pre-stroke mRS.
- Imaging evaluation before randomization: CTP time, occluded vessel, penumbra volume, core infarct volume, and mismatch ratio.
- Randomization stratification information: site number.

- Inclusion and exclusion criteria checklist.
- Randomization information.

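### The primary chi-square test leaves pre-randomization covariates and site unused: it is valid and reaches the planned 80% power, but gives up some efficiency

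*Protocol*

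**What the plan says.** Protocol XI.4 describes the trial as "This study is a 1:1 randomized controlled trial" and names the primary test without qualification: "The Chi-square test is used to compare the primary endpoint between groups". XI.2 sets the frame, "A superiority test will be conducted in this study", at a two-sided 5% level. The sample size in XI.4 assumes that "the rate of primary outcome will be 70% in the study group and 50% in the control group", with "power=80%, assuming a 7% dropout rate", and arrives at 100 patients per arm.

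The log required by VI.10.2 holds date of birth and the NIHSS taken before randomization. It also holds "Imaging evaluation before randomization: CTP time, occluded vessel, penumbra volume, core infarct volume, and mismatch ratio". VI.4.1 admits internal carotid, M1 and M2 occlusions, ages 18 to 85 and any NIHSS above 5. Site is the only stratification factor (Synopsis, VI.6.1). No adjusted analysis of the primary outcome appears in the protocol. XI.3 asks for a description of baseline characteristics and of "the comparability between the study group and the control group".

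**The concern.** The trial collects patient-level baseline data that could plausibly bear on first-pass recanalization and hemorrhage, and balances allocation within site, but the primary test ignores both. If any of these covariates is prognostic, the unadjusted comparison carries outcome variation that could be removed at almost no cost.

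The sample size leaves little slack. Power is 80% only if the 20-point effect holds and dropout stays at 7%, and VI.8.2 does not allow withdrawn participants to be replaced. A modest gain in precision would offset a modest shortfall in evaluable patients. At stake is a few points of power and a somewhat narrower interval. The validity of the test is not in question.

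**Working it through.** **1. The plan's own figure.** Inputs from XI.4 and XI.2: rates 0.70 and 0.50, two-sided α 0.05, power 80%, dropout 7%.

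n per arm = [1.960 × √(2 × 0.60 × 0.40) + 0.842 × √(0.70 × 0.30 + 0.50 × 0.50)]² / 0.20² = (1.358 + 0.571)² / 0.04 ≈ 93. Then 93 / 0.93 = 100 per arm, 200 in total. The figure reproduces exactly for the chi-square without continuity correction. With the correction the result would be 103, or 111 after dropout.

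Power of the chi-square is 80.0% at 93 evaluable per arm, 78.7% at 90 and 76.3% at 85.

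**2. Standard error of the risk difference at 93 per arm.** √[(0.21 + 0.25) / 93] = 7.03 points.

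**3. Approximate effect of adjustment.** Let R² be the share of outcome variance that the covariates explain. The protocol gives no value, so a range is assumed. The variance is scaled by (1 − R²), so the effective size is 93 / (1 − R²):

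| Assumed R² | SE (points) | Power, 93 evaluable per arm | Randomized per arm for 80% power |
|---|---|---|---|
| 0 | 7.03 | 80.0% | 100 |
| 0.02 | 6.96 | 80.8% | 99 |
| 0.05 | 6.85 | 82.0% | 96 |
| 0.10 | 6.67 | 84.0% | 91 |
| 0.15 | 6.48 | 86.1% | 87 |

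**4. Check by simulation.** Both sets use 93 per arm and marginal rates of 50% and 70%.

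- Logistic model with treatment and one prognostic score, 8,000 trials per scenario. Power, chi-square against adjusted: 80.4% and 79.9% (R² 0); 79.9% and 80.7% (0.02); 80.2% and 82.3% (0.05); 79.8% and 84.1% (0.105); 79.4% and 85.9% (0.165). Type I error: 4.7-4.8% for the chi-square, 4.9-5.3% adjusted.
- Standardised risk difference, 3,000 trials per scenario, with assumed ICA/M1/M2 shares of 30/45/25% and one further assumed predictor: 79.7% and 80.6% (R² 0); 79.7% and 81.2% (0.027); 79.4% and 83.1% (0.089); 79.4% and 86.0% (0.166). Type I error: 5.5% and 5.6%.

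The differences at R² 0 go in opposite directions and are of the size of simulation error, √(0.8 × 0.2 / 3,000) = 0.7 points and √(0.8 × 0.2 / 8,000) = 0.4 points. Neither set included site.

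**5. Size of chance imbalance.** With 100 per arm and an assumed ICA share p, the SD of the difference in shares is √[2p(1 − p) / 100]. The chance of a gap of 10 points or more is 7.7%, 12.3% and 14.9% for p = 0.2, 0.3 and 0.4. If success were 20-30 points lower in ICA occlusion (assumed), a 10-point gap would move the raw effect by 0.10 × 20 to 0.10 × 30 = 2-3 points. That is 0.28 to 0.43 of the 7.03-point SE, which already contains this variation.

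**6. Room in the model.** Expected successes are 93 × 0.50 + 93 × 0.70 = 111.6, and failures 186 − 111.6 = 74.4. Treatment, vessel (two terms), NIHSS and age make five parameters, or about 15 failures each. VI.1 plans 10-15 hospitals. Unpooled, these add 9-14 terms and bring this to 74.4 / 14 = 5.3 or 74.4 / 19 = 3.9, which is why small sites need pooling.

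**The case against.** The strongest reply is that nothing here is wrong. The chi-square is a valid test for a randomized two-arm binary comparison. It is the test the sample size was built on, and it reaches the promised power. All of that stands.

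The benefit also rests wholly on an R² that the protocol does not give. An ICA/non-ICA split alone, at the assumed 30% share and 20-30 point gap, gives R² = 0.21 × 0.04 / 0.24 to 0.21 × 0.09 / 0.24, about 4-8%. That is a gain of only 1-3 points of power. The upper end of the range needs further predictors. This also stands, and it limits the size of the point without removing it.

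A reader might infer more than the protocol supports:

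- That vessel, NIHSS and age are strong predictors of this outcome. The protocol reports no association.
- That chance imbalance biases the test or inflates its error rate. It does neither: the imbalance is already in the standard error, and the simulated type I error stays near 5%.
- That the baseline comparability check in XI.3 will decide whether to adjust. XI.3 says nothing of the kind; it is an ordinary description.
- That any adjusted analysis would be post hoc. XIII announces a detailed statistical analysis plan, to be archived before 50 patients are enrolled. It is not at hand, and a supportive adjusted analysis placed there would be prespecified.

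Finally, replacing a documented primary test late in an open-label trial can itself draw criticism. Version 3.1 is dated September 2023, and XV plans follow-up to end in December 2023. This objection stands as a condition on the timing and documentation of the change.

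**Conclusion.** The point holds as a modest, inexpensive improvement. XI.4 fixes an unadjusted comparison although patient-level covariates are on file before randomization and site was used to stratify. If the covariates explain 2-17% of outcome variance, power at 93 evaluable per arm rises from 80% to about 81-86%. If they explain none, essentially nothing is lost and the type I error stays near 5%.

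As a measure of its practical worth, a variance reduction of about 9% would restore power from 76.3% to 80.2% if only 85 per arm were evaluable.

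These figures assume the planned 50% and 70% rates and an R² range that is not in the protocol. They were obtained without site terms. This is a loss of efficiency and not an error or a bias, and a result from the chi-square as planned would be valid.

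**What to change.** In XI.4, make the primary analysis a logistic model with treatment, occluded vessel (ICA / M1 / M2), the NIHSS taken before randomization, age and site. Pool small sites by a rule written down in advance and based on enrollment counts only. Standardise the model over the trial population to a marginal risk difference with a 95% CI, tested at two-sided 0.05. Keep the chi-square as a sensitivity analysis. XI.3 needs no change.

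The change must be made before database lock and before any outcome comparison by arm. It should come from people who have not seen the unblinded data that the monitoring board reviews (XIII), in a dated amendment that says so. If that cannot be documented, the chi-square should stay primary and the adjusted estimate be labeled supportive.

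The cost is slightly more analysis work and the amendment itself. No extra patients or data are needed.
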